## Abstract

**Background:**

There is increasing interest in developing peer-led and 'expert patient'-type interventions, particularly to meet the support and informational needs of those with long term conditions, leading to improved clinical outcomes, and pressure relief on mainstream health services. There is also increasing interest in telephone support, due to its greater accessibility and potential availability than face to face provided support. The evidence base for peer telephone interventions is relatively weak, although such services are widely available as support lines provided by user groups and other charitable services.

**Methods/Design:**

In a 3-arm RCT, participants are allocated to either an intervention group with Telecare service provided by a Diabetes Specialist Nurse (DSN), an intervention group with service provided by a peer supporter (also living with diabetes), or a control group receiving routine care only. All supporters underwent a 2-day training in motivational interviewing, empowerment and active listening skills to provide telephone support over a period of up to 6 months to adults with poorly controlled type 2 diabetes who had been recommended a change in diabetes management (i.e. medication and/or lifestyle changes) by their general practitioner (GP). The primary outcome is self-efficacy; secondary outcomes include HbA1c, total and HDL cholesterol, blood pressure, body mass index, and adherence to treatment. 375 participants (125 in each arm) were sought from GP practices across West Midlands, to detect a difference in self-efficacy scores with an effect size of 0.35, 80% power, and 5% significance level. Adults living with type 2 diabetes, with an HbA1c > 8% and not taking insulin were initially eligible. A protocol change 10 months into the recruitment resulted in a change of eligibility by reducing HbA1c to > 7.4%. Several qualitative studies are being conducted alongside the main RCT to describe patient, telecare supporter and practice nurse experience of the trial.

**Discussion and implications of the research:**

With its focus on self-management and telephone peer support, the intervention being trialled has the potential to support improved self-efficacy and patient experience, improved clinical outcomes and a reduction in diabetes-related complications.

**Trial Registration:**

Current Controlled Trials, ISRCTN63151946

## Background

Numerous studies have reported the relationship between self-management practice for long term conditions, patient behavioural change and subsequent improvement in physical and psychological well being and reduction in health service resource use [1,2]. A review of 145 papers on self management revealed a growing body of evidence demonstrating that compared with standard care, self management approaches improve knowledge, performance of self management behaviours, self efficacy and health status including reduction in blood glucose levels, calorific intake, weight and lowering serum cholesterol [3].

About 2% of the UK population are diagnosed as having diabetes, and the number is predicted to double to over 3 million by 2010 [4]. Diabetes is expensive, accounting for 8–9% of total health service costs in the UK. Much of this relates to the costs of treating the complications of diabetes, such as coronary heart disease and renal failure. Adherence in diabetes has been reported as difficult and complex [5], few patients taking their prescribed regimen entirely as intended [6]. Effective diabetes self-management training interventions have been developed, but the challenge is how to deliver these in a way that is practical, consistent, cost-effective, and acceptable to patients and health care professionals in the 'real world' [7-9]. Adherence can be increased by enabling patients to improve and reinforce understanding, combined with recognition, identification and resolution of obstacles to therapeutic advice [9]. A productive time to intervene to promote adherence is when a new therapy is introduced [10].

The role of the patient in diabetes self-management has expanded beyond responsibility for personal care to incorporate the role of educator. This latter role acknowledges the value of diabetes patient knowledge and experience in the provision of effective education and support. In the UK, in recent years the importance of developing this role has been promoted by health policy. As indicated within the Expert Patient Report [11] research findings 'display the ability of patients to successfully guide other patients in becoming 'expert' in their own care and highlight the value of patient knowledge as an educational and communicative tool'. In line with these observations and combined with the growing awareness of the benefits of lay involvement, the telephone support system of care being tested in this trial incorporated both peer and nurse support.

A potential method of delivering self-management programmes, whether lay or health professional-led, is via telephone contact. A recent Cochrane review has shown that telecommunication for patient care has been found to be acceptable to patients [12]. While telephone contact with patients is a common feature of diabetes specialist nurse practice in the UK, the effectiveness of this is unknown [13], as is the value of telephone support in diabetes care provided by peer supporters. More frequent contact with the healthcare provider may positively affect a patient's adherence to self-management activities [13], enhance autonomy and confidence in managing diabetes [14], and help the healthcare provider and the patient to revise and adjust diabetes management goals [15,16].

In summary, the behavioural change witnessed in patients as a result of improved and supported self-management practice has been associated with a range of physical and psychological benefits. When triangulated with the acceptability and cost effectiveness of telecare and the increasing awareness of the lay advisor role in the successful provision of support, the literature identifies a potentially efficacious, cost effective and patient centred method of enhancing self-management.

### Intervention development and trial design

In line with the MRC framework for development and evaluation of RCTs for complex interventions to improve health [17], the current study proposal has incorporated three key stages of research development. A theoretical basis was established from relevant literature, feasibility work was conducted to develop an understanding of the intervention and its potential outcomes and finally an exploratory trial is being undertaken to determine the requirements of the design and the success of the research strategy.

The feasibility study explored the acceptability and potential benefits of the proposed intervention via qualitative and quantitative research and consultation with expert health professionals [18]. A questionnaire was distributed to 107 GP practices within the Warwick Diabetes Care Research Framework. One hundred percent of responders (N = 82) considered the diabetes telephone care service to be 'highly' or 'very highly' important to the NHS, feasible and of potential benefit to patients. Qualitative interviews were conducted with 7 primary care and secondary care diabetes health professionals. The provision of telephone support to patients experiencing a change in treatment within primary care was considered extremely beneficial and currently, due to inadequate health service resources, a goal which was not being achieved well in either secondary or primary care. Interviewees reported that although telephone support is often provided from secondary care by diabetes specialist nurses (DSN) when patients are first changed to insulin, the short-term nature of this support meant that it had limited effectiveness in assisting patients with the long-term physical and psychological difficulties of treatment change. Additionally, this support is generally not provided to patients experiencing a change from diet to tablets or alteration in type of tablet. Interviewees felt this to be an area requiring greater attention in particular relation to patient difficulty in establishing and maintaining a successful medication regime within their day to day routine.

A needs assessment was also undertaken of self-management of people with a recent diagnosis of diabetes or change in diabetes therapy [19]. The study comprised 6 focus groups conducted with 23 participants recruited within the West Midlands through adverts in local newspapers and leaflets placed in GP clinics. The results clearly identified the perceived potential value of peer support within diabetes patient care. Peer support, facilitated from within the health care system, was felt to represent a valuable untapped resource for furthering and enabling self-management education and support. In addition, expert opinion was sought through the Warwick Diabetes Care Advisory Board, a group of nationally recognised experts of various disciplines related to diabetes care, chaired by [name]. This strongly endorsed the use of peer supporters to advise patients, in light of their knowledge of the current inadequacies in care provision, in particular relation to the ever increasing pressure being placed upon DSNs within secondary care.

Subsequently, a phase I exploratory trial was conducted to test the key components of the telecare intervention including training, recruitment, and practitioner role. The trial consisted of two fully trained peer supporters providing telephone service (shortened version: 2 calls over a 10 day period) to diabetes patients from a single practice experiencing a change in medication (tablet regime). The peer supporters participated in a comprehensive motivational interviewing training programme. The trial was conducted for 1 month and provided telecare support to 7 patients. Telephone record sheets were maintained throughout to ensure consistency of support. Evaluation telephone call interviews revealed that patients felt 'very comfortable' discussing their diabetes care with a peer supporter, were 'very satisfied' with the support received and were happy to receive this support in the future. Reported advantages included speaking to a non health professional who understood diabetes, having someone to listen and the provision of support during a period of uncertainty regarding medication change. Positive outcomes of the exploratory trial were also reported by participating health care professionals and the peer supporters who believed the success of the trial supported the importance of the main study.

### Aims of the Trial

The hypotheses to be tested in this study are that telecare motivational interviewing will be acceptable to patients and primary care health professionals; will be associated with improved social and psychological status; healthier lifestyle choices; and enhanced satisfaction with care.

We propose to:

1. Determine the impact on quality of care, behavioural change and patient responsiveness of a centralised, expert telecare (nurse and peer-led motivational support by telephone) intervention.

2. Compare the impact of nurse and peer supporter telecare provision against routine care.

3. Obtain clinical data as a means to identifying patterns and trends to be used in conjunction with behavioural change outcomes, in order to determine the value of undertaking a full scale RCT of the cost and clinical effectiveness of the intervention.

## Methods/Design

This study is an RCT of three arms:

i. Telecare service provided by diabetes specialist nurses

ii. Telecare service provided by peer supporters

iii. Control group receiving routine care only

Randomisation to control or intervention will be carried out at the patient level. Within the intervention group, patients will be randomly allocated to either a nurse or peer telephone supporter. To limit bias arising from patients' perception of their randomisation, all patients will receive at least one phone call. This should also ensure that the referring healthcare practitioners are as blinded as realistically possible. Patients will not be informed about whether they are in the intervention or control groups. The name, address, telephone number, access times, current treatment, details of any recent change in therapy (medication, diet, monitoring, and physical activity programme) related to diabetes, together with any provisos that were made, will be sent to the trial centre by the referring GP/nurse.

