For patients in an intervention arm of the trial, the first telecare call will be made 3–5 days after referral from the patient's GP. The telecare supporter will tailor (and document) the frequency of subsequent calls to each patient's needs. The 'standard package' will be offering subsequent contact during the periods of days 7–10, 14–18, 28–35, 56–70, 120–150 but some patients will require more frequent contact while others may want less. Before completion of each call, the telecare supporter will negotiate the time of the next call. Supporters will routinely provide feedback on all calls to the research team via a standard form. However, if the telecare supporter feels more immediate contact is required, they will follow a formal feedback process to the GP; for peer supporters this will be a two stage process of referral to nurse and then, where appropriate GP. The reasons for such contact will be documented. Discussion with diabetes specialist nurses who had experience of telephone contact with patients suggested that the mean follow-up call length will be 5–10 minutes. Hence, on average each patient within the intervention groups will receive a total telecare intervention of about 45 minutes duration.

Patients in the control group will receive a single call from a researcher lasting approximately 10 minutes. This call will inform the patient that s/he is allocated to the routine care group, and that is the only phonecall s/he receives. The patient will be encouraged to follow the medical advice given to her/him by the GP/practice nurse.

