#### Outcome Data

All outcome data from patients in the intervention and control groups are being collected at site level by a practice nurse or GP, recorded on templates developed for the purpose, and forwarded by post to the trial office. Patients in the intervention groups will be asked to complete a 4 page questionnaire after 3 and 6 months, while patients in the control group will complete the questionnaire only at 6 months. The questionnaire incorporates The Problem Areas in Diabetes Scale (PAID) [24], the Diabetes Management Self-Efficacy Scale (DMSES) [25], the diabetes self-care activities measure [26], the Perceived Therapeutic Efficacy Scale (scale under development) [27], and an acceptability of service provision measure. The questionnaire will be completed at the surgery and posted in a reply paid envelope.

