#### Clinical Data

Clinical data at baseline will be collected prior to patient randomisation. Blood specimens for HbA1c assessment, total and HDL cholesterol are being taken according to local protocols either by practice staff or the local phlebotomy service. They are being analysed by the local hospital based laboratory services routinely used by the practices, blinded to patient group allocation. We will ensure that if changes in standardisation occur during data collection that, at each site, all data are reported according to the same standard. Practices will arrange a 3 and 6 month review appointment with patients in the intervention group and a 6 month review for those in the control group at which point clinical follow up data will be collected. A reminder of forthcoming appointments will be distributed by the trial office to each participating practice 2 weeks before the appointment is due.

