#### Sample size

The sample size is based upon the primary outcome measure of self efficacy, measured using the DMSES and has been constructed to detect a difference in the primary outcomes of self efficacy perceptions and psychological adjustment. A sample of at least 300 patients (minimum 100 in each arm) has been constructed to detect a difference in self-efficacy scores with an effect size of 0.35, 80% power at a level of 5% significance level [25]. Allowing for an attrition rate of 25% from initial recruitment, we will require 125 subjects in each arm (i.e. 375 participants in total).

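### The protocol says patients will not be told their group, yet its control call tells them; the stated protection against perception bias does not hold for the self-rated primary outcome

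*Protocol article*

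**What the plan says.** Three parts of the protocol article bear on who knows the allocation.

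- **Patients.** Methods/Design gives the reason for calling everyone: "To limit bias arising from patients' perception of their randomisation, all patients will receive at least one phone call". It then adds: "Patients will not be informed about whether they are in the intervention or control groups". The description of the control call, at the end of Proposed Telecare Service, reads: "This call will inform the patient that s/he is allocated to the routine care group, and that is the only phonecall s/he receives".
- **Practitioners.** Methods/Design says of the same universal call: "This should also ensure that the referring healthcare practitioners are as blinded as realistically possible". Clinical Data then sets different visit schedules: "Practices will arrange a 3 and 6 month review appointment with patients in the intervention group", against a 6-month review alone for controls. Outcome Data does the same for the questionnaire: "Patients in the intervention groups will be asked to complete a 4 page questionnaire after 3 and 6 months", against 6 months alone for controls.
- **Laboratory.** Clinical Data says that the local laboratories analysing HbA1c and cholesterol do not know the patient's group. No other blinding is described.

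On the outcome at stake, the Sample size section says: "The sample size is based upon the primary outcome measure of self efficacy, measured using the DMSES". The DMSES and the Problem Areas in Diabetes scale (PAID) are part of the questionnaire that the patient fills in.

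**The concern.** The universal call and the non-disclosure statement are the only measures the protocol offers against patients' knowledge of allocation colouring their answers. Its own control procedure makes that call the moment of disclosure. A researcher who follows the control script breaks the Methods/Design statement, and one who honours the statement cannot deliver the script.

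This matters because the primary outcome has no independent assessor. The patient rates his or her own confidence, and so does the rating on PAID. Someone reading only Methods/Design would conclude that these ratings are shielded from knowledge of the group, when the control patients have been told it outright.

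**Working it through.** No arithmetic settles this point, and the protocol states no figure to reproduce. The check is whether the statements can all be true at once.

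1. **Same patients, same time frame?** The Methods/Design statement covers intervention and control patients without any time limit. The control-call text covers all control patients. Both are written prospectively as current procedure. Neither comes from a summary of changes, and the one amendment that is described concerns the HbA1c threshold.

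2. **Can both be carried out?** No. One rules out telling patients their group, and the other requires telling controls theirs. No section limits or reconciles them.

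3. **Does the safeguard survive in another form?** For controls it does not, because the call that was meant to limit perception bias is the one that reveals the group. For intervention patients the contact pattern itself is informative. After a first call 3–5 days from referral, the protocol says: "The 'standard package' will be offering subsequent contact during the periods of days 7–10, 14–18, 28–35, 56–70, 120–150". That makes 1 + 5 = 6 standard contacts, about 45 minutes in total, against one control call of about 10 minutes. Tailoring can raise or lower the number.

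4. **Can practices infer the group?** Yes, from their own diary. Visits and questionnaires by group are:
   - Intervention: review at 3 and 6 months, questionnaire at 3 and 6 months.
   - Control: review at 6 months, questionnaire at 6 months.

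   Practices book the reviews, and the trial office sends them reminders two weeks ahead. A 3-month appointment therefore identifies an intervention patient. Supporters may also contact the GP about individual intervention patients. Practice staff are the people who collect the outcome data.

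5. **Which outcomes does the remaining blinding cover?** The laboratory's blinding covers the assays for HbA1c and cholesterol, which are secondary. It does not reach the DMSES or PAID, nor the blood pressure and body mass index recorded at the practice.

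**The case against.** The strongest defence is that the protocol claims less than a critic might read into it. It uses the word blinded only for referring practitioners, and with a qualifier. For patients it speaks of limiting bias, and nowhere does it call the trial patient-blinded. That is fair, and it rules out the stronger reading that the protocol claims a patient-blinded trial. What remains is an unqualified non-disclosure statement that the control script contradicts.

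One could also read that statement as covering only what the practice says at referral, before the trial centre calls. The text does not say so, and the statement stands beside the rationale for the call itself.

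A second defence is that telephone support can hardly be masked. Patients receiving repeated calls know that they are supported, and many controls would guess their group from a single call. This also stands. It means the control call should not be held responsible for all of the perception bias. It equally means that the non-disclosure statement could not have delivered much, which is a reason to remove it.

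A reader might go on to infer a particular inflation of the false-positive rate. The documents do not support one. They give no estimate of how far disclosure shifts DMSES scores, do not establish its direction, and offer no way to separate the effect of the disclosure from that of the contact pattern.

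**Conclusion.** The contradiction is real and does not depend on any assumption: the two statements about what patients are told cannot both be followed. The practitioner statement is weakened rather than contradicted, because it is hedged; it rests on the inference that practices notice which patients have a 3-month review.

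The consequence is that DMSES and PAID comparisons with the control group are exposed to reporting bias of unknown size, part of which is inherent in the design. Sample size, randomisation and the planned comparisons are unaffected. This should be fixed because it changes what the trial can say about bias in its primary outcome. It does not show that the primary result will be biased by any given amount.

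**What to change.** Correct the text in the protocol and carry the correction into the trial report:

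- Delete the statement in Methods/Design that patients will not be told their group, so that it agrees with the control call under Proposed Telecare Service.
- Remove the practitioner-blinding statement, or qualify it by noting that the 3-month review and questionnaire reveal allocation to practices.
- Describe the trial as open to patients and practices, with only the laboratory blinded.
- State that the self-rated DMSES and PAID comparisons with control are exposed to reporting bias whose size is not known.

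The cost is a few sentences and a less favourable description of the protection against bias.

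Two further steps are not needed. Rewriting the control call now would give earlier and later controls different calls in a trial that has been running since autumn 2004, and would not restore masking. A rule that the DMSES be read alongside HbA1c is a matter of preference; laboratory blinding protects the assay, but not HbA1c from the actions of patients and practices who know the group.
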